## 1. Background

The advent of Epidermal growth factor receptor (EGFR) - tyrosine kinase inhibitor (TKI), a molecular targeted agent, has triggered a major shift in the treatment of inoperable or recurrent non-small cell lung cancer (NSCLC). Two phase III clinical trials examining the effect of gefitinib as an initial treatment for EGFR mutation positive cases were conducted in Japan, and the results were reported in 2010 in both cases. In the WJTOG3405 trial, which was a comparative study with cisplatin/ docetaxel, the PFS as the main endpoint was 9.2 months versus 6.3 months ( $P < 0.0001$ ), the response rate was 62.1% versus 32.2%, a significantly good result in the gefitinib group was gotten. In addition, in the NEJ002 trial, which was a comparative study with carboplatin/ paclitaxel, the significant prolongations at PFS (10.8 months versus 5.4 months,  $P < 0.0001$ ), and the overall survival (30.5 months vs 23.6 months) were observed. Erlotinib, which is the same type as gefitinib, also showed the significant improvement on PFS in a comparative study with carboplatin/ gemcitabine (Optimal test; 13.1 months versus 4.6 months,  $P < 0.0001$ ). Based on these results, EGFR-TKI is positioned as a very important molecular targeted agent to be used even after the initial treatment or after the second treatment of EGFR mutation positive NSCLC.

On the other hand, recently molecular imaging technology has made dramatic progress with the development of new equipment and measuring methods. The latest mass spectrometer (Imaging Mass Microscope, Shimadzu, Japan) can directly perform molecular imaging using a laser. In other words, since there is no need for radiolabeling and there is no need to homogenate the biological sample, it has the advantage that the distribution of the drug at the tissue and cell level is visualized. Actually, distribution analysis of anti-bacterial agent in an animal model transplanted with *M. tuberculosis*, semi-quantitative mass spectrometry imaging of metabolites of mouse liver transplanted with human colon cancer cells have been reported. However, there are few reports that mass imaging using anticancer drugs was carried out.

Although it is thought that EGFR-TKI binds to the mutated part of EGFR overexpressed in tumor tissues after oral administration, the pharmacokinetics, such as which part of the tumor tissue the EGFR-TKI exactly distributed, is unknown. Imaging Mass Microscope has a high spatial analysis capability, and it is possible to evaluate a combination of tissue morphology information and mass spectrometry. By analyzing the tumor tissue after oral administration of EGFR-TKI, visualization of the EGFR-TKI distribution at the cellular level is expected to be possible. Here, we planned to study the utility of mass spectrometry

imaging using NSCLC surgical specimen of EGFR-TKI patient after oral administration of erlotinib. The purpose of this clinical research is to carry out the world's first mass imaging of EGFR-TKI using an Imaging Mass Microscope that could lead to detailed elucidation of the mechanism of action and tolerance of EGFR-TKI.

## **2. Ethics and compliance**

This study shall be conducted in compliance with the spirit of the Helsinki Declaration (Edinburgh revised edition, 2000) and in accordance with this study protocol.

## **3. Objective**

We perform mass spectrometry imaging of erlotinib using resected non-small cell lung carcinoma after oral administration of erlotinib. We semi-quantitatively identify the presence of erlotinib and its metabolites in tumor tissue/ non-tumor tissue and investigate the mechanism of drug efficacy development.

## **4. Study procedure**

### **4.1. Oral dosing of erlotinib**

Patient diagnosed with EGFR mutation-positive NSCLC and scheduled tumor resection for histology or cytology is registered (N = 1).

Patient receives erlotinib (1 tablet of 150 mg) on the morning of the surgery day (take 6 hours before the start of surgery).

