### **4.2. Measurement of blood erlotinib concentration**

Blood collection is performed at the time of tumor tissue removal, and blood levels of erlotinib and its metabolites are measured. Collect 2 ml in a hemogram test tube and separate it into plasma and blood cell components as soon as possible. Separate plasma and blood cells after separation and quickly store at -20 ° C. Saved samples are anonymized and sent to research cooperation facilities (National Cancer Center Research Institute). Measure the erlotinib concentration in plasma by liquid chromatography tandem mass spectrometry.

Sample destination:

[name]

National Cancer Center Research Institute (NCCRI)

[name]

[contact] [contact]

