### 4.3. Record of administration and blood collection

Describe the following items in the records of drug administration status and pharmacokinetics and store them. For the pharmacokinetic record, send it to the analytical institute (National Cancer Center Research Institute) together with the sample.

- Erlotinib administration day and time
- Tumor tissue excision time
- Blood collection time
- Adverse events appearance

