## **8.2. Administration of protocol drug and schedule of tumor removal**

Erlotinib (Tarceva) is administered according to the schedule described in the Study Procedure section, and the tumor tissue is removed. Tarceba is administered by inversion taking as the guideline after 6 hours of oral administration when it is known that the time of tumor removal is the maximum blood concentration at the time of Tarceva tablet 150 mg single administration oral administration. Regarding adjuvant chemotherapy after surgery, examination will be made according to the results of histopathological examination, not specified.

On the day of the exam (surgery) (an example in the case of conducting surgery in the morning)

AM 7: 00 Tarceva tablet ® 150 mg 1 tablet

AM 8:30 Exit to the operating room

AM 9:30 Surgery started

PM 1:00 Removal of tumor tissue, collection of blood for blood concentration

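### Section 4.1 counts the 6 hours from dose to the start of surgery, Section 8.2 counts them to tumour removal; following 4.1 samples 3.5 h late in the protocol's own example

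*Protocol*

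**What the plan says.** Section 4.1 registers one patient (N = 1), who receives one 150 mg tablet on the morning of the operation. The timing instruction is "take 6 hours before the start of surgery".

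Section 8.2 first states that the drug "is administered according to the schedule described in the Study Procedure section", which is Section 4. It then gives its own timing rule. The English is rough, but the sense is to work back from tumour removal: the drug is "administered by inversion taking as the guideline after 6 hours of oral administration", on the ground that "the time of tumor removal is the maximum blood concentration". The example timetable, given for a morning operation, has the tablet at 07:00, then "AM 9:30 Surgery started" and "PM 1:00 Removal of tumor tissue, collection of blood for blood concentration".

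Section 4.2 ties the plasma sample to the same event: "Blood collection is performed at the time of tumor tissue removal". Section 4.3 requires the dosing time, the "Tumor tissue excision time" and the blood collection time to be recorded.

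**The concern.** The same 6 hours are counted to two different events. In a lung resection the start of surgery and the removal of the tumour are hours apart, so the two rules give different dosing times for the same operation. The only worked timetable in the protocol satisfies one rule and breaks the other.

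The time from dose to removal is the one exposure variable that this study sets on purpose, and Section 8.2 gives the reason: to sample at peak blood concentration. There is one patient, one tablet, one resection and one blood draw. If the team follows Section 4.1 literally, tissue and plasma are taken after the intended peak, and no second patient or later time point can supply the sample that was planned.

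**Working it through.** **Inputs, all from the Section 8.2 example:** dose 07:00; start of surgery 09:30; tumour removal and blood draw 13:00. The rules tested are 6 h from dose to start (Section 4.1) and about 6 h from dose to removal (Section 8.2).

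**Step 1. Check the example against each rule.**
- Dose to removal: 13:00 − 07:00 = 6.0 h. This reproduces the Section 8.2 target.
- Dose to start: 09:30 − 07:00 = 2.5 h. Section 4.1 requires 6 h, so the example breaks it.
- Start to removal, called d: 13:00 − 09:30 = 3.5 h.

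**Step 2. Apply Section 4.1 to the same theatre times.**
- Dose time: 09:30 − 6 h = 03:30.
- Dose to removal: 13:00 − 03:30 = 9.5 h.
- Excess over the target: 9.5 − 6.0 = 3.5 h, which equals d.

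**Step 3. Keep the 07:00 dose and apply Section 4.1.**
- Start of surgery: 07:00 + 6 h = 13:00, the time at which Section 8.2 already has the tumour out.
- Removal with d = 3.5 h: 13:00 + 3.5 h = 16:30, again 9.5 h after the dose.

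**Step 4. General form.** Section 4.1 gives a dose-to-removal interval of 6 + d hours. Section 8.2 gives about 6 hours whatever d is. They agree only if d = 0, that is, if the tumour comes out at the moment surgery starts. The protocol does not fix d. The 3.5 h row below is its example; the other rows are an assumed range.

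| d (h) | Dose to removal under 4.1 (h) | Dose to removal under 8.2 (h) |
|---|---|---|
| 1 | 7 | 6 |
| 2 | 8 | 6 |
| 3 | 9 | 6 |
| 3.5 (example) | 9.5 | 6 |
| 4 | 10 | 6 |
| 5 | 11 | 6 |

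**Step 5. Does the text settle which rule applies?** No order of precedence is stated. The cross-reference in Section 8.2 leads to Section 4, where the only dose-timing instruction is the Section 4.1 sentence. Section 8.2 therefore sends the reader to the rule that its own rationale and timetable contradict.

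**The case against.** The strongest reply is that the intent is clear enough. Section 8.2 is the dedicated dosing section, gives the only rationale and prints the only timetable, and Section 4.2 fits it by placing the blood draw at removal. A reader of both sections would probably take Section 4.1 as the loosely worded line. A 03:30 dose before a 09:30 operation would probably be noticed. Section 8.2 also calls its 6 hours a guideline and sets no window outside which a sample is invalid.

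On consequence, the objective is semi-quantitative identification of erlotinib and its metabolites in tumour and non-tumour tissue. Tumour margin, tumour centre and normal lung all come from the same operation, so a shift in timing applies to all three. No stated analysis depends on sampling at the peak. The actual times are recorded and plasma is measured, so the true interval would be known.

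Much of this stands, and it limits the harm: the error would be visible, and nothing in the document shows that the image would be lost. It does not remove the contradiction. Tolerance around 6 hours from dose to removal does not turn 6 hours from dose to start into the same rule. The timetable is only an example for a morning case. For an afternoon operation the Section 4.1 instruction is workable, and nothing about the hour would warn the team. Recording the times reveals a mistimed dose but does not prevent one.

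**Conclusion.** The inconsistency is real, and Section 4.1 is wrong as written. Followed literally, it delays sampling beyond the Section 8.2 target by the time from start of surgery to removal. That is 3.5 h in the protocol's example (9.5 h against 6.0 h), and 1 to 5 h over the assumed range of d.

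The conclusion rests on reading the awkward sentence in Section 8.2 as aiming for removal about 6 hours after the dose, which the printed clock times confirm. The effect on plasma or tissue concentration cannot be derived, because the document gives no half-life or concentration curve, and none is claimed. The point should be fixed: it concerns the study's single dosing instruction, and with one patient a mistimed sample cannot be replaced.

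**What to change.** In Section 4.1, replace the timing phrase with: *take 6 hours before the planned time of tumour removal*. This agrees with the rationale and timetable in Section 8.2 and makes that section's reference back to Section 4 correct.

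Report the achieved dose-to-removal interval alongside the imaging and plasma results, using the times that Section 4.3 already collects.

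The cost is one reworded sentence, with no added procedure, sample or data item.

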### **4.2. Measurement of blood erlotinib concentration**

Blood collection is performed at the time of tumor tissue removal, and blood levels of erlotinib and its metabolites are measured. Collect 2 ml in a hemogram test tube and separate it into plasma and blood cell components as soon as possible. Separate plasma and blood cells after separation and quickly store at -20 ° C. Saved samples are anonymized and sent to research cooperation facilities (National Cancer Center Research Institute). Measure the erlotinib concentration in plasma by liquid chromatography tandem mass spectrometry.

Sample destination:

[name]

National Cancer Center Research Institute (NCCRI)

[name]

[contact] [contact]

### 4.3. Record of administration and blood collection

Describe the following items in the records of drug administration status and pharmacokinetics and store them. For the pharmacokinetic record, send it to the analytical institute (National Cancer Center Research Institute) together with the sample.

- Erlotinib administration day and time
- Tumor tissue excision time
- Blood collection time
- Adverse events appearance

### 4.4. Handling of excised tumor tissue

Tumor tissues removed by surgery should be frozen by liquid nitrogen as quickly as possible and stored at -80 ° C. The stored tissues are sent to the analytical institute (National Cancer Center Research Institute). The specimens of 1 cube centimeter or more of the marginal part and the center part of the tumor as well as the part considered as normal lung, are sent, respectively.

### 4.5. Analysis: mass spectrometry imaging of erlotinib

Mass spectrometry imaging of erlotinib in tissues is carried out using an iMScope (Shimadzu, Kyoto, Japan).

## 5. Indication

### 5.1. Inclusion criteria

- Histologically or cytologically proven diagnosis of Non-small-lung cancer
- EGFR mutation positive
- Stage I–IIIA, operable
- Eastern Cooperative Oncology Group (ECOG) PS 0-1
- Adequate organ and marrow function defined as follows

$$\text{WBC} \geq 4,000/\mu\text{L}, \text{ANC} \geq 2,000/\mu\text{L}$$

$$\text{Platelets} \geq 100,000/\text{mm}^3 (100 \times 10^9/\text{L})$$

Hemoglobin  $\geq 9$  g/dL (90 g/L)

Serum creatinine  $\leq$  ULN or estimated creatinine clearance  $\geq 90$  ml/min as calculated using the method standard for the institution

Total serum bilirubin  $\leq$  ULN

AST and/or ALT  $\leq$  ULN

PaO2  $\geq 80$  mmHg or SpO2  $\geq 95\%$

- Evidence of a personally signed and dated informed consent document indicating that the patient has been informed of all pertinent aspects of the study

## **5.2. Exclusion criteria**

- Smoking history
- Lung disease such as emphysema, fibrosis, organized by image examination that is not related to cancer
- Obstructive or restrictive pulmonary disorders
- Case with serious complications
- Severe infection
- Severe comorbidities
- Patients who received any chemotherapy or radiotherapy
- Known or possible hypersensitivity to the drug that may increase the risk associated with study participation
- Patients who are pregnant or lactating. Patients of childbearing potential
- Case in which the doctor in charge judged inappropriate

## **6. Patient Information and consent**

### **6.1. Description using document**

Prior to registration of the case in this study, the attending physician will explain sufficiently to the patient and its families deemed appropriate as subjects using the explanatory documents on the following matters. In doing so, give enough time to ask questions and to decide whether to participate in the study.

- Purpose and method of this study
- Expected effects and adverse event and its treatment
- Do not receive disadvantages even if you do not agree to participate in the study
- Be able to withdraw this from anytime even after agreeing to participate in the study
- Other necessary matters concerning human rights protection of patients

## **6.2. Acquisition of consent using documents**

After explanation using the explanatory document, when consent based on the patient's free willing is obtained about participation in this study, obtain the signature and consent date of the patient in the consent form integrated with the explanation. The doctor who explained will sign the consent form and state the date of consent. The written agreement will be in three copies, some of it will be stored in the electronic medical record and some will be delivered to the patient.

## **6.3. Withdraw consent**

If document agreement is obtained and then consent is withdrawn, record the date and the reason for withdrawal of consent.

## **7. Registration, treatment start, progress report and end report**

### **7.1. Registration**

If there is a case judged to be able to be registered (a case that satisfies the inclusion criteria and does not fall under the exclusion criteria), the attending physician obtains consent from the document and then contacts the study corresponding investigator.

### **7.2. Treatment start, progress report, and discontinuation/ termination report**

The treatment contents performed in this study is defined as protocol treatment. The doctor in charge of study informs the study responsible doctor as appropriate the initiation, progress report, and completion report of the protocol treatment and always conducts it while taking cooperation.

## **8. Intervention method**

### **8.1. Protocol drug**

Erlotinib (trade name; Tarceva tablet ® )

Refer to the package insert for drug handling. Study drugs are purchased from Chugai Pharmaceutical under the research expenses by the Research Director and administered to the subjects.

## **8.2. Administration of protocol drug and schedule of tumor removal**

Erlotinib (Tarceva) is administered according to the schedule described in the Study Procedure section, and the tumor tissue is removed. Tarceba is administered by inversion taking as the guideline after 6 hours of oral administration when it is known that the time of tumor removal is the maximum blood concentration at the time of Tarceva tablet 150 mg single administration oral administration. Regarding adjuvant chemotherapy after surgery, examination will be made according to the results of histopathological examination, not specified.

On the day of the exam (surgery) (an example in the case of conducting surgery in the morning)

AM 7: 00 Tarceva tablet ® 150 mg 1 tablet

AM 8:30 Exit to the operating room

AM 9:30 Surgery started

PM 1:00 Removal of tumor tissue, collection of blood for blood concentration

## **8.3. Monitoring toxicity**

Although this study is a single administration of the protocol drug, toxicity monitoring is also carried out just after the tumor extirpation surgery. Adverse events admitted within 2 weeks from erlotinib intake day (surgery day) and its NCI-CTCAE grade are all recorded. In order to grasp the signs of interstitial pneumonia at an early stage, SpO2 monitor and appropriate chest X-ray photograph are carried out for 5 days after surgery. Also, blood tests should be conducted to check for liver function abnormalities as a rough guide for 1 week after administration.

## **9. Observation items**

The study physician performs the following observation and examination and fills out the result in the data sheet and the chart.

### **9.1. Background: before administration for protocol drug**

- ① Patient identification code (registration number)
- ② Date of document consent acquisition
- ③ Age (at registration)
- ④ Sex
- ⑤ Height
- ⑥ Body weight
- ⑦ Medical history
- ⑧ Complications (excluding accompanying symptoms due to the original disease)
- ⑨ Drug allergy
- ⑩ Clinical diagnosis, definitive diagnosis method (tissue diagnosis or cell diagnosis)
- ⑪ Stage classification (at initial diagnosis), TNM classification

## **9.2. Blood biochemical examination**

Before administration of Tarceva (on the day of surgery or the day before surgery), days 2, 4, 7 after surgery.

Hemoglobin, white blood cell count, leukocyte fraction, number of platelets

Total bilirubin, direct bilirubin, AST, ALT,  $\gamma$ -GTP, LDH, ALP, CRP

## **9.3. Self symptoms and medical examination findings**

Before administration of Tarceva (before surgery), daily until 7th day after surgery

Diarrhea, fever, rash, dyspnea

## **10. Evaluation of safety**

For adverse events occurring during treatment of this protocol (from the day of Tarceva administration to 1 week after surgery), all grade, time of onset, outcome etc. should be indicated on the treatment record sheet. Grade evaluation follows the Japanese translation of NCI Common Toxicity Criteria (NCI - CTC) Version 4.0 JCOG version.

## **11. Obligation to report adverse events**

### **11.1. Expedited report**

#### **11.1.1. Object of expedited report**

All of the following adverse events that occurred during this clinical trial are subject to

expedited report.

- ① All deaths that occurred within 7 days from the day of protocol treatment and study drug administration
- ② Mortality that can not deny the causal relationship with protocol treatment after 7 days from the day of administration of the study drug
- ③ Serious adverse event not anticipated
- ④ Acute lung injury

#### **11.1.2. Procedure of expedited report**

The doctor in charge of study and the investigator will report according to the following procedure.

- ① Primary report: The doctor in charge of the study reports the first report to the investigator as soon as possible after knowing the occurrence of the adverse event. In addition, the study physician will prepare as a separate sheet "Detailed case report details (A4 free format)" with detailed information written within 7 days, submit it to the investigator and the department manager in charge. At that time, since we prioritize the transmission of information promptly, there may be places that are undetermined and can not be entered in the report.
- ② Secondary Report: The investigator will prepare a detailed "Adverse Event Report" as a rule within 15 days from knowing the occurrence of the adverse event and report it to the person in charge of the department concerned and the safety evaluation committee.
- ③ Additional report: In case of information (eg autopsy report in the case of death) since the secondary report or blank entry in the secondary report, each person in charge of department and safety report to the safety evaluation committee.

#### **11.1.3. Definition of severity and expectancy**

Among adverse events, the following are serious adverse events.

- ① Those leading to death
- ② Threatening life
- ③ Requiring hospitalization for treatment or extension of hospitalization period
- ④ Persistent or obvious failure or malfunction
- ⑤ Those causing birth defects

- ⑥ Even if the above result is not reached, in a serious event such as subjecting the subject to extreme crisis or requiring treatment so that the result as described above is not reached, or an event having a possibility of leading to these What the physician deems serious

### **11.2. Regular report**

Regarding the following adverse events, a "regular report" is conducted in accordance with the secondary report of the express report.

- ① Adverse events of Grade 2, Grade 3 that are not anticipated (not listed in "side effects" of drug package insert)
- ② An adverse event of Grade 3, 4 (as described in "side effects" of drug package insert) expected
- ③ Other serious medical events (those judged by the attending physician as important information to be shared within the research group)

